## Abstract

**Background:**

The COVID-19 pandemic has negatively affected the mental health of international migrant workers (IMWs). IMWs experience multiple barriers to accessing mental health care. Two scalable interventions developed by the World Health Organization (WHO) were adapted to address some of these barriers: Doing What Matters in times of stress (DWM), a guided self-help web application, and Problem Management Plus (PM +), a brief facilitator-led program to enhance coping skills. This study examines whether DWM and PM + remotely delivered as a stepped-care programme (DWM/PM +) is effective and cost-effective in reducing psychological distress, among Polish migrant workers with psychological distress living in the Netherlands.

**Methods:**

The stepped-care DWM/PM + intervention will be tested in a two-arm, parallel-group, randomized controlled trial (RCT) among adult Polish migrant workers with self-reported psychological distress (Kessler Psychological Distress Scale; K10 > 15.9). Participants (*n* = 212) will be randomized into either the intervention group that receives DWM/PM + with psychological first aid (PFA) and care-as-usual (enhanced care-as-usual or eCAU), or into the control group that receives PFA and eCAU-only (1:1 allocation ratio). Baseline, 1-week post-DWM (week 7), 1-week post-PM + (week 13), and follow-up (week 21) self-reported assessments will be conducted. The primary outcome is psychological distress, assessed with the Patient Health Questionnaire Anxiety and Depression Scale (PHQ-ADS). Secondary outcomes are self-reported symptoms of depression, anxiety, posttraumatic stress disorder (PTSD), resilience, quality of life, and cost-effectiveness. In a process evaluation, stakeholders’ views on barriers and facilitators to the implementation of DWM/PM + will be evaluated.

**Discussion:**

To our knowledge, this is one of the first RCTs that combines two scalable, psychosocial WHO interventions into a stepped-care programme for migrant populations. If proven to be effective, this may bridge the mental health treatment gap IMWs experience.

**Trial registration:**

Dutch trial register NL9630, 20/07/2021, https://www.onderzoekmetmensen.nl/en/trial/27052

**Supplementary Information:**

The online version contains supplementary material available at 10.1186/s12888-023-05288-5.

## Introduction

Large-scale epidemics of infectious diseases have been associated with a substantial burden on the mental health of the population [1]. Although recent studies have not found convincing evidence for substantial increases in mental health symptoms during the COVID-19 pandemic compared to the pre-pandemic period [2], trajectory studies show that the mental health of vulnerable groups such as women, young people, people with pre-existing physical ill-health, or those experiencing socioeconomic difficulties deteriorated more than the general population during the COVID-19 pandemic [3, 4].

International migrant workers (IMWs) can be viewed as another group vulnerable to the consequences of the COVID-19 pandemic. IMWs are migrants of working age, who at some point were part of the labour force of the country they migrated to [5]. Globally, there are 169 million IMWs, of which two-thirds reside in high-income countries [5]. In the Netherlands, there are about one million IMWs, with over half of them coming from the European Union, primarily from Poland (CBS, 2022). IMWs often have a vulnerable position in society, working in so-called 3-D jobs: dirty, dangerous, and demanding (or demeaning or degrading) jobs [6]. Compared to non-migrant workers, IMWs are more likely to work in essential, low-skilled occupations, have temporary contracts, work longer hours for lower wages, are willing to take on greater risks and have jobs that are not suitable for remote working [6, 7]. Most often, they work in the service sector (e.g. wholesale and retail, transportation and storage), followed by industry and agriculture [5]. During the pandemic, additional challenges for IMWs were, amongst others, limited social protection, high risk of exposure to and transmission of COVID-19, and impending job loss, in turn, leading to economic hardship and loss of housing (often provided by the employer) [8].

Prior to the COVID-19 pandemic, mental health problems were already one of the most commonly reported work-related health problems among IMWs [9, 10]. IMWs have been found to develop more symptoms of anxiety and depression than non-migrant workers [11]. These common mental health problems have been exacerbated by the ongoing COVID-19 pandemic [12]. Despite this mental health burden, access to specialist health care is limited [10, 13]. IMWs can face various barriers related to seeking mental health services (e.g. lack of awareness of services, stigma) and to accessing the existing services (e.g. language differences, lack of culturally appropriate services) [14, 15]. In light of the COVID-19 pandemic, there is thus an even higher need for psychosocial interventions for IMWs targeting the most notable symptoms of psychological distress, such as anxiety, depression, and posttraumatic stress disorder (PTSD) [16, 17].

Scalable strategies and interventions such as those developed by the World Health Organization (WHO) may bridge the mental health treatment gap in vulnerable populations such as IMWs. These interventions are scalable because they are simplified and short versions of evidence-based psychological interventions for common mental disorders and can be delivered as (guided) self-help interventions (e.g. a book or online format) and/or by trained and supervised non-specialist mental health care workers [18, 19]. Since the onset of the COVID-19 pandemic, there has been growing shift to the remote delivery of mental health services due to physical distancing and lockdowns [4]. Human-guided digital interventions seem to be equally effective to face-to-face psychotherapy for the treatment of common mental health symptoms such as anxiety and depression [20]. Policy makers, mental health professionals and service users have expressed interest in continuing with this remote delivery in the absence of pandemic-related measures [21].

For this study, two WHO scalable interventions have been combined to be delivered remotely as a stepped-care intervention. In stepped-care interventions, individuals first receive an evidence-based, low-intensity treatment, i.e. a treatment requiring less of the individual’s and the professional’s time and which is less expensive [22]. As patients’ progress is monitored, those not (significantly) responding to treatment step up to a treatment of higher intensity [22]. In this way, stepped-care interventions have the potential to reach more people at the cost of fewer resources. Often, (guided) self-help treatments are used as a first step in stepped-care interventions, showing comparable effectiveness to face-to-face interventions [23].

In this RCT of IMWs in the Netherlands, participants in the intervention group are offered a two-step, stepped-care intervention. The first step is a digitalized guided self-help web application (web app) of Doing What Matters in times of stress (DWM), an illustrated self-help book that is part of Self-Help Plus (SH +) [24]. SH + is a guided self-help intervention based on acceptance and commitment therapy (ACT) that is delivered in five 2-h sessions to groups of 20–30 people. So far, SH + has been evaluated among refugee populations, showing overall beneficial effects in improving self-identified problems and well-being [25]. For this project, DWM has been adapted for delivery in a digital smartphone-based format [26]. The second step is Problem Management Plus (PM +), a transdiagnostic psychological intervention based on cognitive behavioural therapy (CBT) that addresses common mental health problems (e.g. depression, anxiety, stress) and self-identified practical problems (e.g. unemployment). Over five weekly face-to-face remotely delivered videoconferencing sessions, PM + teaches strategies to manage psychosocial problems [27]. In previous randomized controlled trials (RCTs), PM + has been found to be effective in reducing psychological distress in low-income settings [28, 29] and Syrian refugees in the Netherlands [30, 31]. In addition to DWM and PM + , all participants, i.e. participants in both the intervention and control group, receive psychological first aid (PFA). PFA consists of humane, supportive, and practical help for individuals who have experienced a traumatic event [32]. This stepped-care programme has also been found to be effective among healthcare workers experiencing psychological distress in the initial pandemic hotspots [33].

Recent advances have been made in examining both digital markers and biomarkers either as correlates or as secondary treatment outcomes. Traditional assessment of psychological well-being and distress in IMWs through (online) questionnaires can be burdensome and time-consuming, while recently developed non-invasive, low-burden digital phenotyping measures that integrate voice, speech, movement and facial expression data from smart devices (e.g. smartphones) may be a promising and scalable way for assessing psychological wellbeing (e.g. depression, PTSD) [34–36]. Notably, altered speech and vocality, reduced facial expressivity and movement have been found in major depressive disorder and psychopharmacological treatment has demonstrated restored levels of digital markers (e.g. increased head movement) and a decrease in anger and fear facial expressions [37, 38]. Similarly, neuroendocrine correlates such as cortisol can be used as a non-invasive biomarker of physiological responses to chronic stressors. Hair cortisol concentrations (HCC) reflect hormone release over longer time intervals, as they indicate hormone secretion over several months [39]. Studies have found that HCC is related to PTSD, depression and anxiety disorders [40, 41] or with perceived job insecurity and work stress [42, 43]. In recent years, HCC has also been used as a secondary outcome of psychological interventions [44, 45].

This paper presents the study protocol for a randomised controlled trial in the Netherlands to examine the (cost-)effectiveness of the remotely delivered stepped-care DWM/PM + programme adapted for distressed IMWs living in the Netherlands. The final stage will consist of a process evaluation to assess the feasibility and acceptability of the intervention.

## Methods

### Study aim and design

This study is part of the EU Horizon2020 RESPOND project, which aims to improve the preparedness of European mental health care systems in the face of future pandemics. The primary objective of the current study is to evaluate the (cost-)effectiveness, feasibility, and acceptability of the culturally and contextually adapted DWM/PM + stepped-care program among Polish migrant workers living in the Netherlands throughout the COVID-19 pandemic in terms of mental health outcomes, resilience, wellbeing, and costs to health systems and society. This will be done by conducting a single-blind, two-arm, parallel-group, superiority RCT with a 1:1 allocation ratio in which a remotely delivered stepped-care programme with PFA and care-as-usual (enhanced care-as-usual or eCAU) will be compared to PFA with CAU (eCAU) only. The primary endpoint is a composite measure of depression and anxiety at 21 weeks from baseline assessment (*t*_4_). Figure 1 shows a flowchart of the study design. In addition, we will explore barriers and facilitators to treatment engagement and adherence and opportunities for scaling up among IMWs in the Netherlands, as well as the implementation outcomes of the stepped-care programme. This will be done by a mixed-methods process evaluation following the RCT.

**Fig. 1 Fig1:**
[figure not shown]
Flowchart of the randomized controlled trial

### Study setting

This study takes place in the Netherlands and is conducted by VU University Amsterdam in collaboration with a local mental health care organisation specialized in the delivery of mental health care to Polish people [GGZ Keizersgracht]. The DWM/PM + programme is delivered fully remotely in the participants’ language (i.e. Polish); both participants and those delivering the intervention join the programme from their own (private or work) environments.

### Participants

#### Inclusion criteria

age 18 years or older;currently living in the Netherlands (no duration of stay required; they may have arrived after most pandemic restrictions had been lifted);having psychological distress, as indicated by the Kessler Psychological Distress Scale (K10) with a score of > 15.9 (see screening measure);having sufficient mastery (written and spoken) of the language in which the programme is delivered (i.e. Polish);having access to an electronic device with Internet access to follow the programme.

#### Exclusion criteria

planning to permanently move abroad within the next 6 months, i.e. before the last quantitative assessment;having acute medical conditions (requiring hospitalization);imminent suicide risk, or expressed acute needs or protection risks requiring immediate follow-up;having a severe mental disorder (e.g. psychotic disorder, substance dependence);having a severe cognitive impairment (e.g. severe intellectual disability, dementia);receiving specialist psychological treatment (e.g. eye movement desensitization and reprocessing, CBT);using psychotropic medication for less than 2 months or change in dosage in the past 2 months.

### Procedure

#### Recruitment

Participants will be recruited in various ways, e.g. through NGOs, general practitioners, municipalities, Polish churches, Polish supermarkets, and social media (e.g. Facebook, Instagram). To avoid potential coercion, people interested in participating in the project are invited to reach out to the research team themselves (i.e. by e-mail, telephone, or through social media). Once they reached out, the research team contacts all potential participants by phone. If they are interested, both a digital and paper informed consent form (ICF) will be sent. Permission to record DWM phone calls and/or PM + sessions for fidelity checks and digital marker analysis, and/or to provide a hair sample (see other measures), are all optional.

Once the participant has given informed consent, an online screening session is scheduled. All participants that indicate on the ICF that they are willing to give a hair sample will receive a hair sample kit consisting of instructions on how to take the hair sample, a (paper) hair questionnaire, and a prepaid envelope to return it.

#### Screening

Screening (*t*_0_) will be conducted through a video call (MS Teams, 20–30 min) with a Polish speaking research assistant. Screening consists of an online self-report questionnaire (sociodemographic questions and K10) followed by exclusion questions that are asked directly to the participant (e.g., “did you receive any mental health diagnosis?”) or answered by the research assistant (e.g., “does the participant follow the conversation?”). Screening is ended as soon as a participant screens out based on any inclusion or exclusion criterion. Participants who indicated on the ICF that they were willing to give a hair sample but score too low on the K10 are still asked to give a hair sample at baseline and to complete the baseline assessment (*t*_1_).

#### Assessments

After screening, data is collected through self-report assessments at four time points: *t*_1_ (baseline, week 1 – sent at the end of screening), *t*_2_ (post-DWM, week 7), *t*_3_ (post-PM + , week 13), and *t*_4_ (follow-up, week 21) with the online programme Castor Electronic Data Capture (EDC) [46]. Each digital assessment with questionnaires will be sent to participants via e-mail and can be completed through any device with Internet access (e.g. smartphone, laptop, tablet). Total completion time of each digital assessment is about 30 min (see ‘Study measures’).

Participants have 14 days to complete the questionnaire When an assessment remains incomplete, participants will receive a maximum of 3 reminders on days 2, 5, and 10 through different communication channels to promote participant retention. Hair samples and (paper) questionnaires are collected at *t*_1_ and *t*_4_ through regular mail. Once the research team receives the hair sample and the hair questionnaire, answers are entered in Castor EDC as well. Participants receive a 10-euro gift voucher for each completed assessment with a maximum of 4 vouchers (*t*_1_-*t*_4_), regardless of whether they send a hair sample.

#### Assessors

The consent and screening procedure will be carried out by trained research assistants who are fluent in Polish. Research assistants will be blinded to participant allocation to the intervention or control group, by restricting their user rights in Castor EDC. This way, they can assist participants during the assessments if needed. Blinding may be revealed in case of suicidal ideation (see screening measures).

#### Randomization

Participants (*N *= 212) will be randomized into the PFA/DWM/PM + CAU (intervention) (*n *= 106) or PFA/CAU only (control) (*n* = 106) group using a four and six block design via Castor EDC.

#### Trial status

This RCT started enrolling on 03 June 2022. Currently, 138 participants have been enrolled.

#### Process evaluation

After the RCT, participants who gave permission for follow-up research will be approached to participate in the process evaluation. A qualitative process evaluation will be conducted to assess the satisfaction and acceptability of the DWM/PM + programme and to identify barriers and facilitators to treatment engagement and adherence. Additionally, this evaluation aims to explore opportunities for scaling up the implementation of the DWM/PM + programme for IMWs within the existing healthcare system. This evaluation will be conducted through semi-structured interviews with key informants, including DWM/PM + participants (*n* = 20), family members/close persons of participants (*n* = 12), and stakeholders (e.g. (mental) health practitioners, policy makers). DWM/PM + participants will consist of participants who completed DWM and improved, who completed PM + and improved, who completed PM + and did not improve, who dropped out during DWM, and who dropped-out during PM + . Additionally, a focus group discussion (FGD) will be conducted with helpers and trainers/supervisors (*n* = 6–8) (see *‘*Stepped-care programme*’*). Participants from the RCT and their family members/close friends will each receive a 20 euro gift voucher per interview.

### Study measures

Table 1 provides an overview of all study measures. Participants need to complete the items of the K10, the primary outcome (PHQ-ADS), and the suicide screening, in order to continue the assessment. The rest of the questionnaires are non-mandartory and participants can skip items and sections.

**Table 1 Tab1:**
[figure not shown]
Schedule of enrolment, interventions and assessments

#### Screening measures

Psychological distress will be measured with the K10 [47]. The K10 consists of ten items that focus on anxiety and depression-related distress over the past 30 days. Items are scored on a five-point Likert scale (1–5), giving a total score of 10–50 with higher scores representing higher levels of distress. In line with previous research [48, 49] a cut-off score of > 15.9 is used, which indicates psychological distress [50]. The K10 is validated in various languages (e.g. Dutch) [51].

 Suicidal ideation will be assessed with the suicidal thoughts interview from the PM + manual (*t*_0_*,* screening) [52] or with a screening question used in a previous trial testing an e-health intervention (*t*_2_-*t*_4_) [53]. If a participant answers positively to this screening question (*t*_2_-*t*_4_), a message will appear with information on where to get help and stating that a member of the research team will reach out to the participant. Once a phone call has been scheduled with the participant, an assessor will administer the suicidality module of the Mini-International Neuropsychiatric Interview (MINI) [54]. Suicidal ideation is not assessed during *t*_1_ as this directly follows screening. Cognitive impairment will be assessed with the observation checklist from the PM + manual.

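### The reason for skipping the suicide check at t1 does not fit low-K10 hair donors, who by the stated screening order would leave before the t0 interview

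*Protocol article*

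**What the plan says.** Five statements in the protocol article bear on this point.

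- **Eligibility.** One inclusion criterion is "having psychological distress, as indicated by the Kessler Psychological Distress Scale (K10) with a score of > 15.9". One exclusion criterion is "imminent suicide risk, or expressed acute needs or protection risks requiring immediate follow-up".
- **Order of screening (t0).** "Screening consists of an online self-report questionnaire (sociodemographic questions and K10) followed by exclusion questions that are asked directly to the participant", or that the research assistant answers.
- **Stop rule.** "Screening is ended as soon as a participant screens out based on any inclusion or exclusion criterion".
- **Exception.** In the same section, people who agreed to give hair but "score too low on the K10 are still asked to give a hair sample at baseline and to complete the baseline assessment". Under Assessments, that baseline assessment (t1) is "sent at the end of screening".
- **Suicide checks.** Under Screening measures, ideation is assessed at t0 with an interview from the PM+ manual. At t2 to t4 it is assessed with a screening question, backed by a help message and a call from the team. It is not assessed at t1, "as this directly follows screening".

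The Study measures section adds that the PHQ-ADS items must be completed before a participant can continue an assessment.

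**The concern.** The reason for leaving the check out of t1 assumes that everyone who reaches t1 has just had the t0 interview. Low-K10 hair donors reach t1 by another route: they fail an inclusion criterion, screening ends, and they are still asked for hair and for t1. If the interview belongs with the exclusion questions, they have not had it.

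What is at stake is participant safety and the consistency of a safety procedure. These people have consented and are asked to complete a mandatory measure of depression and anxiety. No estimate, test or power figure in the trial depends on the answer.

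**Working it through.** There is no plan figure to reproduce. The check traces two people through the stated procedure.

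**Who is affected.** The K10 has ten items scored 1 to 5, so totals are whole numbers from 10 to 50. Inclusion needs more than 15.9, so the first qualifying total is 16 and the failing totals are 10 to 15.

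**Where the t0 interview sits.** The Screening section lists two contents for the self-report questionnaire: sociodemographic questions and the K10. The suicidal thoughts interview is neither of these. It is an interview, and it informs an exclusion criterion. Both facts place it in the second step, with the exclusion questions. This is an inference, because the section does not name the interview.

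**The two paths.**

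| Step | Randomised participant (K10 of 16 or more) | Hair donor with K10 of 10 to 15 |
|---|---|---|
| K10 | passes | fails the inclusion criterion |
| Stop rule | not triggered | screening ends |
| Exclusion questions, including the interview (inferred) | reached | not reached |
| t1, sent at the end of screening | completed | still requested |
| Suicide check within t1 | none | none |
| Suicide checks described before or at t1 | 1 | 0 |

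**Does the exception restore the interview?** It names two things, the hair sample and t1. It does not mention the remaining exclusion questions.

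**Does anything else fill the gap?**

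- *Mandatory suicide screening (Study measures).* This applies where the screening is given, and Screening measures says it is not given at t1.
- *The Psychological First Aid call.* It comes two to five days after screening, whereas t1 is sent when screening ends. Its description includes no suicidality check. It is also unclear whether the call extends to people who have screened out.
- *Later assessments.* The exception asks these donors only for baseline hair and t1. No t2 to t4 contact is described for them, so the checks at those visits do not reach them.

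For participants who pass screening, the stated reason holds in full.

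**The case against.** The strongest reply is that no sentence says low-K10 donors miss the interview. The Screening section gives only two examples of exclusion questions and does not place the interview. Screening measures says ideation will be assessed at t0 without limiting this to people above the K10 threshold. The schedule in Table 1 was not available. The stop rule is already relaxed for this group, and the two items named in the exception may not be a complete list. The reason for omitting the check reads as written for enrolled participants, for whom it is correct. A journal article may also leave the safety handling of non-randomised donors to the full protocol. Finally, people below the distress threshold are at low risk, and one function of the t0 check is to decide eligibility, which no longer matters for them.

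Much of this stands. The position of the interview is inferred, giving it to everyone at t0 is not ruled out, and the risk is probably low. Two parts do not stand.

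- The article is not merely silent. It states an order, a stop rule, an exception and a reason, and these four do not fit together. If every donor does get the interview, practice departs from the order and stop rule as written.
- The trial does not treat a low K10 as a substitute for asking. The t2 to t4 question is described with no K10 condition, although scores may have fallen to 15 or below by then; the t2 K10 is used to decide who is offered step 2.

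**Conclusion.** The concern holds and is minor. Followed as written, the procedure gives a hair donor with a K10 of 10 to 15 no described suicide check, against one before t1 for a randomised participant. The reason offered for omitting the check at t1 does not apply to that donor.

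This rests on two assumptions: that the t0 interview is held with the exclusion questions, and that Table 1 does not say otherwise. Confidence is therefore moderate. The number of such donors is not stated, so no count of people affected can be given. They are not part of the randomised comparison, and the effect on the primary analysis is nil.

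**What to change.** For low-K10 hair donors only, do one of the following:

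1. hold the t0 suicidal thoughts interview during the screening call, before the t1 link is sent; or
2. add to their t1 the screening question, help message and call-back already used at t2 to t4.

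Then amend the reason given under Screening measures so that it covers only people who completed screening, and name the added check in the exception under Screening. If these donors already receive the interview at t0, the Screening section should say so.

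The cost is low. The first option adds a few minutes to a video call already under way. The second reuses existing material and brings occasional call-backs. The Trial status section says "Currently, 138 participants have been enrolled", against a target of 212, so recruitment was still open. The change would reach only people screened after it is made.
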